**STATISTICAL considerations**

Sample size justification

The sample size was calculated based on an assumption that relapse rates would be 30% in the chloroquine only group and 4% in the 14 day primaquine group.

To allow for 20% loss to follow up or incomplete data, a total of 50 patients per arm will be recruited to detect such a difference with 95% confidence and 80% power. The groups will be compasred by survival analysis..

Statistical Analyses

Proportional data

These will be compared using chi squared or Fisher’s exact test, as appropriate. Crude proportions will be calculated with the exact 95% confidence intervals (CI), where relevant.

Continuous data

These will be summarised by medians (IQR, ranges) and means (standard deviations, 95% CIs), as appropriate, and will include the parasite counts and laboratory parameters. Comparisons of continuous data will be assessed using the paired/unpaired t tests or the sign rank/Mann Whitney U tests, as appropriate.

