**OBJECTIVES**

*Primary Objective*

To compare the effectiveness of primaquine 0.25mg base/kg/day given for 5 days versus 14 days together with a standard chloroquine regimen in *P*. vivax malaria.

*Secondary Objectives*

To measure the clinical and parasitological responses with chloroquine alone and two chloroquine –primaquine regimens.

To assess safety and tolerability of the different regimens

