**TRIAL DESIGN**

Study sites

*Summary of Trial Design*

This will be a prospective open label comparison of chloroquine (CQ) alone versus CQ plus 5 days unobserved primaquine or CQ plus 14 days unobserved primaquine in patients with acute vivax malaria in Kolkota. Patients will be followed for 15 months and primary and recurrent infections were genotyped.

Study duration; **2 years**

*Primary and Secondary Endpoints*

Primary Endpoint

Recurrence rate of vivax malaria over 15 months

Secondary Endpoints

Parasite clearance time assessed by microscopy

Fever clearance time (i.e. the time taken for the tympanic temperature to fall below 37˚C and remain there for at least 24 hours)

Genotype assessments Parasite clearance time assessed by microscopy

*Trial Participants*

Overall Description of Trial Participants

Male and non-pregnant female patients aged between 36 months and 65 years with acute uncomplicated vivax malaria are the target study population. All study patients must meet the applicable inclusion and exclusion criteria.

I*nclusion Criteria*

- Male or female, aged from 36 months to 65 years old, inclusive
- Acute uncomplicated *P. vivax* malaria, confirmed by positive blood smear with asexual forms of *P. vivax*
- Fever defined as > 37.5°C tympanic temperature or a history of fever within the last 24 hours
- Written informed consent (by legally acceptable representative in case of children)
- Willingness and ability of the patients/guardians to comply with the study protocol for the duration of the study

*Exclusion Criteria*

- Signs of severe/complicated malaria (WHO, 2000)
- Haematocrit < 25% or haemoglobin (Hb) < 8 g/dL at enrollment
- Acute illness other than malaria requiring treatment
- For females: pregnancy, breast feeding
- Patients who have received antiamalrial treatment within the previous 7 days
- History of allergy or known contraindication to study drugs
- G6PD deficiency;patients who are deficient on spot testing will not be allocated to the two primaquine groups.

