Subjects who fulfil all the inclusion criteria and have none of the exclusion criteria will be randomised 1:1;1 to one of the three treatment arms. Allocation will be done by drawing the next sequential numbered opaque envelope, which contains the study number of the patient referring to the study treatment. The subjects will be assigned a study arm through a computer-generated randomisation scheduleThis is an open-label study so the blinding of investigators and patients is not applicable. However, the randomisation procedure allows for adequate drug allocation concealment before envelopes are opened. All laboratory investigations will be performed without knowledge of the treatment allocation.

*Blood sampling*

On admission

On study admission, immediately before drug administration, blood will be collected for the following:

- parasite count
- EDTA 2mL whole blood sample for PCR parasite genotyping
- haematocrit

G6PD spot test

*Study drug regimens*

(1) chloroquine (25mg base /kg total) only

(2) chloroquine (25mg base /kg total) followed by primaquine 0.25mg base/kg/ day for five days

(3) chloroquine (25mg base/kg total) followed by primaquine 0.25mg base/kg/ day for 14 days

*For recurrences:*

chloroquine (25mg base /kg total) followed by primaquine 0.25mg base/kg daily for 21 days.

The first dose will be observed but all subsequent antimalarial doses will be taken at home. Each patient will be instructed on the need to complete the full course of treatment.

*Follow up procedures*

Patients will be seen daily until a febrile then weekly for one month and thereafter every one to two months for 15 months. If vivax malaria recurs blood will be taken for parasite genotyping and comparison with the original infection.

*Additional visits*

Patients presenting to the clinic with a fever or other symptoms on unscheduled days will be assessed by the study physician. Their temperature will be recorded and blood smear will be made for any patient with a documented fever (oral or tympanic temperature ≥ 37.5˚C) or a history of fever. Patients will be treated as clinically indicated.

Patients with recurrent parasitaemia

Patients with a recurrent parasitaemia during follow up will have blood taken for the following:

- parasite speciation and count
- haematocrit
- if parasitaemic: EDTA 2mL whole blood sample for PCR parasite genotyping

*Discontinuation/ Withdrawal of Participants from the Study*

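### For parasite and fever clearance times, combine the 5-day and 14-day primaquine arms and adjust for admission values: the two arms are prescribed the same treatment through primaquine day 5

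*Protocol*

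**What the plan says.** The Secondary Objectives (Protocol, Objectives) set out "To measure the clinical and parasitological responses with chloroquine alone and two chloroquine –primaquine regimens". The Secondary Endpoints (Trial Design) include "Parasite clearance time assessed by microscopy" and fever clearance time, defined as "the time taken for the tympanic temperature to fall below 37˚C and remain there for at least 24 hours".

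Of the three regimens (Procedures, Study drug regimens), the first is chloroquine alone at a fixed total dose per kg. The shorter primaquine arm is listed as "2) chloroquine (25mg base /kg total) followed by primaquine 0.25mg base/kg/ day for five days". The longer arm has the same chloroquine total and the same daily primaquine dose, continued for 14 days.

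Under Statistical considerations, the paragraph on continuous data says that the summaries "will include the parasite counts and laboratory parameters", and then: "Comparisons of continuous data will be assessed using the paired/unpaired t tests or the sign rank/Mann Whitney U tests, as appropriate". No covariate adjustment is mentioned. Survival analysis appears only in the sample size paragraph, which concerns relapse.

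The protocol gives no number of chloroquine days, no start day for primaquine and no expected clearance time.

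**The concern.** Clearance times describe the acute response to treatment. The 5-day and 14-day arms diverge only from the sixth primaquine day. A difference in clearance reached before that day cannot come from primaquine doses that have not yet been taken. If the by-regimen framing is carried into the analysis with the stated two-sample tests, two things follow. A positive 5- versus 14-day result would be open to misreading as an effect of course length. And 100 patients with the same prescribed early treatment would be reported as two groups of 50, each with a needlessly wide interval.

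The stated tests also leave out the admission parasite count and admission temperature. Both are collected before treatment and are natural predictors of how long clearance takes.

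**Working it through.** **The plan's own figure.** The only size stated is 50 per arm, for relapse of 30% versus 4%, 80% power and 20% loss. With a two-sided 5% level and mean proportion 0.17:
- n = [1.960·√(2·0.17·0.83) + 0.842·√(0.30·0.70 + 0.04·0.96)]² / 0.26² = 31.6, that is 32 per arm
- with continuity correction, 39 per arm
- 39 / 0.80 = 48.75, that is 49

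The stated 50 is therefore reproduced to within one patient. It concerns recurrence and says nothing for or against the handling of clearance times.

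**Prescribed treatment, side by side (Study drug regimens).**

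| Period | CQ alone | CQ + 5-day PQ | CQ + 14-day PQ |
|---|---|---|---|
| Chloroquine total | 25 mg base/kg | same | same |
| Primaquine days 1–5 | none | 0.25 mg base/kg/day | same as 5-day arm |
| Primaquine days 6–14 | none | none | 0.25 mg base/kg/day |

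The two primaquine arms differ only in the last 14 − 5 = 9 days. Chloroquine alone differs from both from whenever primaquine starts, and that day is not stated.

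**Precision of mean clearance time.** The SD is not in the documents, so half-widths are in SD units: half-width = t(0.975, N−1)/√N.
- N = 50 (one arm): 0.284 SD
- N = 100 (both primaquine arms): 0.198 SD; 0.198/0.284 = 0.70, so 30% narrower
- N = 150 (all patients): 0.161 SD; 0.161/0.284 = 0.57, so 43% narrower

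If the full 20% loss applied to these endpoints, the first two figures would be 0.320 SD (N = 40) and 0.223 SD (N = 80), and the gain would still be 30%.

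**Chloroquine alone versus primaquine.** The SE is proportional to √(1/n₁ + 1/n₂).
- 50 v 50: √(2/50) = 0.200
- 50 v 100: √(1/50 + 1/100) = 0.173
- Ratio 0.866, so 13% smaller

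**Adjustment for the admission value.** The SE is multiplied by √(1 − r²), where r is the correlation of the admission value with clearance time. The documents give no r; assuming 0.3 to 0.6:
- r = 0.3: √0.91 = 0.954, about 5% smaller
- r = 0.6: √0.64 = 0.80, 20% smaller

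**False positives, only if all three pairs are tested.** With no true difference and 50 per arm, simulation of three pairwise t tests at 5% (normal data, 40,000 runs) gives at least one positive in 12.4% of trials per endpoint. The protocol does not specify these three tests, so this shows what such a choice would cost. It is not an error rate of the plan.

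**The case against.** The strongest reply is that the protocol never assigns a test to clearance times. The objective is to measure responses, the rule for continuous data is generic and leaves the test to judgement, and pooling or covariate adjustment may be settled in an analysis plan that is not shown. This stands in part. No 5- versus 14-day clearance test and no set of three pairwise tests is written down, so the point cannot be put as a stated error. What remains is that the protocol frames the response by regimen and offers only unadjusted tests for comparing continuous data, and a better rule costs almost nothing.

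Three stronger readings are tempting and are not supported:

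- *That any difference between arms is chance, including chloroquine alone.* This would need clearance to end before primaquine starts, and the protocol gives neither time. In addition, the Exclusion Criteria in Trial Design can be read as keeping G6PD-deficient patients out of the primaquine groups only. The Synopsis excludes severe deficiency, and the randomisation text admits only patients with no exclusion criterion. Until these are reconciled, the chloroquine-alone arm may differ systematically.
- *That a 5- versus 14-day difference could only be a false positive.* The identity is one of prescribed treatment. The trial is open-label and only the first dose is observed, so adherence could differ by arm.
- *That the plan tests admission parasite counts between arms.* Parasite counts are named in the sentence on summaries. Neither admission nor a between-arm comparison is mentioned there, and the paired tests listed could serve within-patient comparisons, since counts and haematocrit are taken again at recurrence.

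It may also be said that chloroquine alone versus combined primaquine could itself be close to null. It could, which is why the contrast is offered only for the case where a between-arm comparison is wanted.

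**Conclusion.** The point holds as a modest improvement to the secondary analyses. Combining the two primaquine arms for clearance times narrows the interval for the mean by about 30% (0.284 to 0.198 SD) and removes a comparison that cannot inform on course length. This rests on clearance being complete by primaquine day 5, which is assumed because the documents give no clearance times. The 30% is for a mean with a common SD.

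Adjustment for the admission value would reduce the SE by a further 5–20%, depending wholly on the assumed correlation of 0.3–0.6. The 43% gain from pooling all 150 patients should not be claimed as firm, because it needs the chloroquine-alone arm to be comparable in both early treatment and eligibility. The primary comparison of recurrence is unaffected.

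**What to change.** Add to the continuous data paragraph of Statistical considerations:

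- For parasite and fever clearance times, the 5-day and 14-day primaquine arms are combined and are not tested against each other.
- Any between-arm comparison is chloroquine alone versus the combined primaquine arms, by regression with log10 admission parasite count as covariate for parasite clearance, and admission temperature for fever clearance.
- An all-patient summary may be given in addition, as description only.

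Before the chloroquine-alone arm is compared or pooled, reconcile the statements on G6PD-deficient patients in the Synopsis, the Exclusion Criteria and the randomisation text, and state when primaquine starts relative to chloroquine.

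The cost is a few sentences and no new data: the admission parasite count and temperature are already collected. What is given up is a separate 5- versus 14-day clearance test.

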**ETHICS**

Declaration of Helsinki

The Investigator will ensure that this study is conducted in compliance with the Declaration of Helsinki

ICH Guidelines for Good Clinical Practice

The Investigator will ensure that this study is conducted according to any National Regulations and that it will follow the principles of the ICH Guidelines for Good Clinical Practice 1996.

Approvals

The study protocol and its associated documents will be submitted to the appropriate local ethics committees for written approval.

The Investigator will submit and, where necessary, obtain approval from the above parties for all substantial amendments to the original approved documents.

Risks

This study will use drugs that have been studied thoroughly and their toxicities are well described. In general, they are all well tolerated.

Benefits

Benefits of Treatment

Malaria is a disease that needs to be treated promptly. All patients will benefit from receiving efficacious treatment at no cost. They will be followed up closely and will be given rescue treatment if clinically indicated.

Alternatives to Study Participation

Subjects are able to decline freely participation in this study. If so, they will receive standard care for their malaria.

Confidentiality

The trial staff will ensure that the participants’ anonymity is maintained. All documents will be stored securely and be accessible to trial staff and authorised personnel only.

**DATA HANDLING AND RECORD KEEPING**

All study data will be recorded on a standard Case Report Forms (CRF. The participants will be identified by a study specific participant number and/or code in any database. The name and any other identifying detail will NOT be included in any study data electronic file. Data may be used alone or in combination with data from related studies in secondary analyses.

**SPONSORSHIP**

The Faculty of Tropical Medicine is the study sponsor.

**PUBLICATION POLICY**

Any data published in the peer-reviewed medical literature will protect the identity of the subjects. This trial will be registered in a web based protocol registration scheme. All those who have made a substantial contribution will be co authors on publications.

